#### 8.3.5 ADVERSE EVENT REPORTING

All adverse events (AEs) will be reported to the participating site's responsible Research Ethics Board (REB) in accordance with the participating site's AE reporting guidelines (e.g. *CAREB Guidance on Reporting Unanticipated Problems including Adverse Events to Research Ethics Boards*). The site or co-investigator will assess each adverse event in terms of its expectedness and relationship to the study drug. Information to be collected will include an event description, date of onset, investigator/clinician's assessment of severity, relationship to study product

(assessed by the site investigator), and date of resolution/stabilization of the event and event outcome (resolved/recovered, recovered with sequelae, not recovered/not resolved, death, or unknown).

The following Disease Related Events (DREs) will not be reported per the standard reporting process described above.

- Hospitalization for IV rehydration OR gastroenteritis like symptoms
- Future health care provider visit, ED return visit for vomiting, diarrhea, or dehydration
- IV rehydration
- Nausea
- Loss of appetite
- Abdominal pain, distension, bloating
- Vomiting, diarrhea, fever, flatulence
- Rash or Diaper Rash
- Any event that was present at enrollment during the review of systems and that has not worsened (i.e. not new since enrollment in the study).

The events listed above are part of the natural history of the underlying disease process of acute gastroenteritis in children and will be recorded on study CRFs or in note-to-files, as applicable.

*Adverse Event reporting procedures can be found in the study TMOP.*

---

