#### Warnings and Precautions:

- QT interval prolongation and Torsades de Pointes: Avoid in patients with congenital long QT syndrome; monitor with electrocardiograms (ECGs) if concomitant electrolyte abnormalities, cardiac failure or arrhythmias, or use of other QT prolonging drugs;
- Serotonin syndrome: Reported with 5-HT3 receptor antagonists alone but particularly with concomitant use of serotonergic drugs;
- Masking of progressive ileus and/or gastric distention following abdominal surgery or chemotherapy-induced nausea and vomiting

Adverse reactions most frequently reported are headache, constipation, feeling of warmth, and flushing. There have been rare reports of tachycardia, angina (chest pain), bradycardia, hypotension, syncope, electrocardiographic alterations, seizures, rash, and hypersensitivity reactions.

Taking in to account our carefully chosen inclusion and exclusion criteria, the risk of adverse events is low in the population of children who will be enrolled in this study. Given the broad use of ondansetron, and the potential benefit associated with the outpatient use of this medication following ED discharge, it is vital that we determine if any benefit is accrued related to its use.

---

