#### 8.3.4 TIME PERIOD AND FREQUENCY FOR EVENT ASSESSMENT AND FOLLOW-UP

The occurrence of an adverse event (AE) or serious adverse event (SAE) may come to the attention of study personnel during the follow-up questionnaires performed with caregivers or if a study participant presents for medical care to the enrolling ED, or upon review of data by a study monitor.

All AEs including local and systemic reactions not meeting the criteria for SAEs will be captured on the appropriate case report form (CRF). Information to be collected includes an event description, date and time of onset, clinician's assessment of severity, relationship to study product (assessed only by those with the training and authority to make a diagnosis), and date and time of resolution/stabilization of the event.

Any medical condition that is present at the time the participant is screened will be considered as baseline and not reported as an AE. However, if the study participant's condition deteriorates at any time during the study, it will be recorded as an AE.

Changes in the severity of an AE will be documented to allow an assessment of the duration of the event at each level of severity to be performed. AEs characterized as intermittent require documentation of onset and duration of each episode.

Study staff and the site or co-investigator will record all reportable events with start dates occurring any time after informed consent is obtained until 7 (for non-serious AEs) or 15 days (for SAEs) after the last day of study participation.

During each follow up contact made, the investigator/study staff will inquire about the occurrence of AE/SAEs since the last contact (via telephone or email). Events will be followed for outcome information until resolution or stabilization.

As listed in section 1.3 Schedule of Activities, Adverse Events will be assessed via telephone or email contact with the caregiver 24, 48, and 168 hours after enrollment in the study. Possible Adverse Events will be assessed using open-ended feedback questions on the follow-up questionnaires. Trained research study staff will review the response provided by the caregiver and will follow up by telephone as soon as possible. Details regarding the event will be obtained via telephone and contact will be made daily, or weekly, as required to obtain the resolution/stabilization details.

---

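### Section 8.3.5 exempts every rash, not only diaper rash, from standard adverse event reporting, although the protocol names rash as an ondansetron reaction and plans no other comparison of it

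*Combined protocol and SAP*

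**What the plan says.** Section 8.3.5 first sets out the standard process. Adverse events go to the site's research ethics board, and "The site or co-investigator will assess each adverse event in terms of its expectedness and relationship to the study drug". Severity, dates and outcome are also collected. The section then makes an exception: "The following Disease Related Events (DREs) will not be reported per the standard reporting process described above". The list that follows includes "Rash or Diaper Rash". Only its last bullet is qualified; that bullet covers events already present at enrolment that have not worsened. The listed events are described as natural history of gastroenteritis and "will be recorded on study CRFs or in note-to-files, as applicable".

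Section 2.3.1, under Warnings and Precautions, gives rare reports with ondansetron that include "electrocardiographic alterations, seizures, rash, and hypersensitivity reactions". Section 8.3.3.2 requires the relationship to study intervention to be assessed for all adverse events and says that the study product must always be under suspicion.

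Section 9.4.4 plans adverse event summaries by MedDRA System Organ Class and Preferred Term, with intensity and relationship. It names seven safety outcomes, and rash is not one of them. It does not say whether disease-related events enter the summaries. It also limits the included adverse events to those that start between randomization and discharge.

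**The concern.** The exemption sorts rash by cause before anyone has looked at the cause. A child who develops a generalised or urticarial rash after a home dose fits the entry as written, because nothing in it refers to type of rash, timing after a dose, or suspicion of the drug. A site that follows section 8.3.5 may write a note-to-file and stop there.

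Section 4.1 makes the adverse event profile part of what the trial compares, and the safety row of Table 1.0 sets adverse events against placebo as an objective. If rash of possible drug or excipient origin is handled as disease at some sites and as an adverse event at others, the relatedness tables will be incomplete. A modest difference between arms in non-serious rash might then never be tabulated.

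**Working it through.** No arithmetic applies. The documents give no expected rate of rash, and the point rests on no sample size or error rate. The check is a comparison of sections.

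1. **Scope of the entry.** Section 8.3.5 names rash and diaper rash as alternatives. If only diaper rash were meant, the first word would be redundant. The limit to unchanged baseline events sits in a separate bullet and does not restrict this one. So a new or worsened rash of any kind is on the list.

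2. **What the exemption removes.** The process described above the list consists of ethics board reporting and the investigator's assessment of expectedness and relationship, with severity, dates and outcome. For listed events only some record is required, and a note-to-file suffices. A note-to-file has no required field for relationship, severity or onset relative to dosing.

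3. **Conflict with the risk section.** Compare the section 8.3.5 list with the adverse reactions in section 2.3.1 (headache, constipation, warmth, flushing, and the rare cardiac, neurological, skin and hypersensitivity reports). Rash is the one item on both lists: section 2.3.1 treats it as a possible drug reaction, section 8.3.5 as disease.

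4. **Conflict with the causality rule.** Section 8.3.1 defines an adverse event as any adverse occurrence, caused by the drug or not, so a new rash after a study dose qualifies. Section 8.3.3.2 then requires its relationship to be assessed. Section 8.3.5 takes it out of the process in which that is done. Two sites could each follow the protocol and handle the same rash differently.

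5. **Other routes to an arm comparison.**

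| Event on the exempt list | Where else it is analysed |
|---|---|
| Vomiting | Secondary outcomes, section 9.4.3; severity score component |
| Diarrhea | Safety outcomes, section 9.4.4; severity score component |
| Intravenous rehydration | Secondary outcome, section 9.4.3; severity score component |
| Revisits | Secondary outcome, section 9.4.3; severity score component |
| Fever, hospitalization | Severity score components, Table 3.0 |
| Rash | None named |

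For rash, the MedDRA tables are the only planned route, and section 9.4.4 does not say that exempt events enter them.

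6. **The window in section 9.4.4.** Study doses are given at home, no sooner than 8 hours after the clinical dose (sections 1.1 and 1.3). Read literally, a summary restricted to events before discharge would leave out most events after study doses, whether exempt or not. Correcting the rash entry alone would therefore not bring these rashes into the tables.

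**The case against.** Much of the case on the other side stands.

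- **The events are not discarded.** Section 8.3.5 keeps a record, and where that record is a CRF, rash can be compared by arm. Section 9.4.4 has any answer to the open-ended question followed up by telephone, and section 7.1 lets the investigator decide that an adverse event report is needed for a clinically significant finding. A reader might infer that the trial cannot show a rash difference at all. The documents do not support that; they show only that nothing ensures assessment or comparison. A telephone discussion with a trained team member is not the investigator's causality assessment, and section 7.1 is discretionary.
- **Serious and allergic reactions stay reportable.** Section 8.3.6 covers serious events whether or not related, hypersensitivity is not on the exempt list, and section 5.2 excludes known allergy to either product. The exclusion lowers the risk without removing it. The gap is confined to non-serious rash.
- **Distension is a different matter.** The list also contains "Abdominal pain, distension, bloating", and section 2.3.1 warns of "Masking of progressive ileus and/or gastric distention". It is tempting to treat this as a second conflict. The warning is tied to abdominal surgery and to chemotherapy-induced vomiting, and it concerns masking of a condition. The trial enrols previously healthy children with gastroenteritis. The documents give no ground for removing distension from the list.
- **Section 8.3.4 is not contradicted for new rash.** Its words, "condition deteriorates at any time during the study, it will be recorded as an AE", follow a sentence about conditions present at screening. They concern worsening from baseline.
- **The DSMB loses nothing that this process gave it.** The standard process in section 8.3.5 reports to ethics boards; section 8.3.6 sends serious events to the DSMB. The DSMB's data elements are set separately (section 10.1.6), and it may ask for more detailed tables.
- **Most rashes may be viral.** That is an argument for blinded assessment of each one, and does not justify exempting all of them.
- **Detailed procedures are in the trial manual,** which is not among the documents. It may narrow the entry, but the protocol text would still need to agree with it.

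**Conclusion.** The point holds for rash. Section 8.3.5 exempts all rash from causality-assessed adverse event reporting, against sections 2.3.1 and 8.3.3.2, and no planned analysis is certain to compare it by arm. Its reach is every non-serious rash other than diaper rash among the 1030 children to be randomized. How many that is cannot be derived: the documents give no all-cause rate and describe drug-related reports as rare, so any count would be a guess and would mix viral rashes with drug reactions. The efficacy analyses are untouched.

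The conclusion assumes that the unqualified word means any rash and that the trial manual does not narrow it. This is a worthwhile, low-cost correction to a stated rule; it does not threaten the trial's main result.

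**What to change.** 1. In section 8.3.5, narrow the entry to diaper rash alone.
2. Record any other rash that is new or worse since the enrolment review of systems as an adverse event, with severity, relationship and expectedness assessed while blinded.
3. In section 9.4.4, state that disease-related events are captured on a structured CRF and tabulated by arm.
4. In the same section, reconcile the limit to events before discharge with dosing at home, so that events after study doses enter the tables.
5. Re-code rashes already on CRFs or in note-to-files while still blinded and before the database is closed (section 9.4.9), as far as the records allow. Report how many could not be classified.

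The cost is some extra adverse event forms for viral rashes in both arms, an amendment that needs ethics board approval before use, and re-coding work at six sites that will be harder where only a note-to-file exists. Eligibility, dosing, sample size and the efficacy analyses do not change.

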### 8.3.6 SERIOUS ADVERSE EVENT REPORTING

Any AE considered to be serious by the Principal Investigator or Site Investigator or which meets the definition of an SAE included in section 8.3.2 must be reported to the lead site/Principal Investigator and the study Data Safety and Monitoring Board (DSMB), in accordance with the DSMB charter reporting requirements.

The site investigator/clinician will immediately report to the principal investigator/sponsor any serious adverse drug reaction or adverse event, whether or not considered study intervention related, including those listed in the protocol or product monograph and must include an assessment of whether there is a reasonable possibility that the study intervention caused the event. Study endpoints that are serious adverse events (e.g. all-cause mortality) must be reported in accordance with the protocol unless there is evidence suggesting a causal relationship between the study intervention and the event (e.g. death from anaphylaxis). In that case, the site investigator must immediately report the event to the principal investigator/sponsor.

Reports of Serious Adverse Events and/or Serious Adverse Drug Reactions must be reported to the lead site within 48 hours of the site-investigator becoming aware of the event. Event details should be captured on the appropriate study CRF.

The principal investigator/sponsor is required to inform Health Canada of any serious, unexpected adverse drug reaction (ADR) that has occurred inside or outside Canada. ADR reports must be filed:

- where the ADR is neither fatal nor life-threatening, within 15 days after becoming aware of the information
- where it is fatal or life-threatening, immediately where possible and, in any event, within 7 days after becoming aware of the information
- within 8 days after having informed Health Canada of the ADR, submit as complete as possible, a report which includes an assessment of the importance and implication of any finding

Where the adverse drug reaction is neither fatal nor life-threatening, the sponsor will notify Health Canada and all participating investigators of the event and any potential serious risks, from clinical trials or any other source, as soon as possible, but in no case later than 15 calendar days after the sponsor determines that the information qualifies for reporting.

Each ADR which is subject to expedited reporting should be reported individually in accordance with the Health Canada / ICH Guidance Document E2A: Clinical Safety Data Management: Definitions and Standards for Expedited Reporting.

A completed ADR Expedited Reporting Summary Form should be attached to the front of the completed ADR report – suggested report format: Suspect Adverse Reaction Report - CIOMS form of the Council for International Organizations of Medical Sciences. The report should be submitted by fax or email to the appropriate regulatory directorate.

All serious adverse events (SAEs) will be followed until satisfactory resolution or until the site investigator deems the event to be chronic or the participant is stable. Other supporting documentation of the event may be requested by the lead site/Principal Investigator and should be provided as soon as possible.

SAEs will be reported to the participating and lead site's responsible REB in accordance with the institutional REB Serious Adverse Event reporting guidelines (e.g. *CAREB Guidance on Reporting Unanticipated Problems including Adverse Events to Research Ethics Boards*):

- If the SAE is considered life threatening or fatal, a report must be submitted within 7 calendar days of the investigator becoming aware of the event.
- For all other SAEs, a report must be submitted within 15 calendar days of the investigator becoming aware of the event(s).

---

### 8.3.7 REPORTING EVENTS TO PARTICIPANTS

All study participants, or their caregivers, will be notified if at any time new findings become available which may be in the best medical interest of the study participant or impact their willingness to continue participation in the study.

---

### 8.3.8 EVENTS OF SPECIAL INTEREST

Not applicable.

---

### 8.3.9 REPORTING OF PREGNANCY

The possibility of pregnancy occurring in this population while the participant is on protocol and taking the study intervention is exceedingly unlikely given the age range of the participants and their illness status. Given the routine use of ondansetron in pregnant women, and the duration of study medication administration, pregnancy screening is not indicated. In fact, ondansetron use in the US in 2014 had reached 22% with the greatest amount of use occurring in the first trimester.

Nevertheless, if by remote chance the participant tests positive on a pregnancy test and notifies the study team, the site investigator will be notified immediately. The site investigator will then make an informed decision

regarding the continuation of the study medication. The site investigator may contact the medical monitor for additional support, as applicable. Pregnancy tests will not be administered by the study team and therefore it will be up to the participant/caregiver to notify the study team of a positive pregnancy test.

The pregnancy will be the responsibility of the participant and their treating physician, not the study team. Safety information and a study information sheet is provided to the participant and their caregiver at time of enrollment; which should be shared with the participant's treating physician by the participant/caregiver.

Pregnancy will not be reported as an Adverse Event. Reports of pregnancy will be sent to local Research Ethics Boards, as dictated by local institutional policy.

## 8.4 UNANTICIPATED PROBLEMS

### 8.4.1 DEFINITION OF UNANTICIPATED PROBLEMS (UP)

Unanticipated problems are problems involving risks to participants or others to include, in general, any incident, experience, or outcome that meets **all** of the following criteria:

- Unexpected regarding nature, severity, or frequency given (a) the research procedures that are described in the protocol-related documents, such as the Research Ethics Board (REB) approved research protocol and informed consent document; and (b) the characteristics of the participant population being studied;
- Related or possibly related to participation in the research ("possibly related" means there is a reasonable possibility that the incident, experience, or outcome may have been caused by the procedures involved in the research); and
- Suggests that the research places participants or others at a greater risk of harm (including physical, psychological, economic, or social harm) than was previously known or recognized.

### 8.4.2 UNANTICIPATED PROBLEM REPORTING

The investigator will report unanticipated problems (UPs) to the reviewing REB and the Data Coordinating Center (WCHRI-DCC), principal investigator (PI), and Network Coordinator (NC). The UP report will include the following information:

- Protocol identifying information: protocol title and number, PI's name, and the REB project number;
- A detailed description of the event, incident, experience, or outcome;
- An explanation of the basis for determining that the event, incident, experience, or outcome represent a UP;
- A description of any changes to the protocol or other corrective actions that have been taken or are proposed in response to the UP.

To satisfy the requirement for prompt reporting, UPs will be reported using the following timeline:

- UPs that are serious adverse events (SAEs) will be reported to the REB, and the WCHRI- DCC/study sponsor within 7 days of the site-investigator becoming aware of the event.
- Any other UP will be reported to the REB and the WCHRI-DCC/study sponsor within 15 days of the site investigator becoming aware of the problem.
- All UPs should be reported to appropriate institutional officials (as required by an institution's written reporting procedures).

*Additional information regarding reporting procedures (signatories, format, etc.) can be found in the study TMOP and SOP documentation.*

### 8.4.3 REPORTING UNANTICIPATED PROBLEMS TO PARTICIPANTS

All study participants/caregivers will be notified of any new Unanticipated Problems (UP) which may affect the participant's current or future willingness to participate in the study.

Participants/caregivers will be notified individually by telephone or email, based on their chosen follow-up preference and the study team's ability to confirm the individual has received the information.

## 9 STATISTICAL CONSIDERATIONS

### 9.1 STATISTICAL HYPOTHESES

The primary objective is to determine if the use of multi-dose oral ondansetron compared with placebo, provided at ED discharge, will result in a reduction in the proportion of children with moderate to severe disease following discharge as reflected by a MVS score  $\geq 9$ .

### 9.2 SAMPLE SIZE DETERMINATION

The primary analysis will be performed on a binary outcome: Development of moderate-to-severe disease. The power of this analysis is based on the proportion of patients with moderate-to-severe disease. Our pilot data indicate that 30% of patients will have moderate to severe disease following the index visit (personal communication with [name]). Furthermore, expert surveys indicated that an absolute risk reduction of 10% would constitute a minimal clinically-important difference (MCID). Therefore, our sample size calculation assumed a 30% event rate in the control group for which we desire to detect an absolute beneficial treatment effect of 10% with 90% power. Using a two-sided type I error of 0.05 and the hypothesized proportions yields a required total sample size of 784 patients. Our expected power, should we find different event rates in our 2 groups, is displayed in Table 2.0.

